## Objectives {7}

The ability to retrieve specific memories is a cognitive and emotional protective factor. Thus, developing and improving techniques that facilitate the generation of such memories, which are able to enhance mood state, could be highly effective in the prevention and/or reduction of depressive symptoms in healthy older adults. Consequently, the aim of the present study is to delve deeper into the knowledge and effectiveness of different visual stimuli in inducing positive emotions and reducing negative emotions, examining how the level of personal relevance of pictures as autobiographical memory cues may affect an individual’s emotion regulation. Importantly, this new knowledge could also be used in interventions focused on the training of specific positive memories with the aim of improving its efficacy in the treatment of clinical depression in the elderly population.

Additionally, given the differences in emotion regulation between young and older adults, we aim to assess whether the influence on emotion regulation of the level of personal relevance of the images differs according to a person’s age.

The main aim of this study, then, is to experimentally evaluate how the level of personal relevance of the images used as stimuli to access specific positive autobiographical memories can improve emotion regulation, especially in older adults. From this primary aim, we derive the following specific objectives:
To experimentally study the impact of the personal relevance of pictures on the improvement of mood state, following negative mood induction. To this end, we will use three types of images, classified according to their personal relevance: (a) personal autobiographical photographs (high personal relevance), (b) images of locations related to the participants’ lives (medium personal relevance) and (c) images from the IAPS (low personal relevance).Additionally, as suggested by Talarico et al. [82], events remembered with a high sense of reliving induce stronger emotions. For this reason, we will also examine the degree of reliving in the autobiographical memories evoked by the three types of images.To analyse any age-related differences in the effectiveness of the use of the three types of images to regulate emotion. We will compare the efficacy of the three categories of pictures (high, medium and low relevance) in inducing positive mood states in a group of young adults and a group of older adults.

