##### Control questions following exposure to the pictures/photographs

To assess the extent to which the participant felt involved in viewing the images chosen to elicit positive affect, the following questions are included: (1) On a scale from 0 to 9, indicate your level of concentration when recalling the event (0 = total lack of concentration; 9 = total concentration), and (2) on a scale from 0 to 9, indicate to what degree you were able to relive the positive emotions you felt at the moment of the event (0 = I was unable to relive the emotions; 9 = I was able to relive the emotions completely).

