## Statistical methods

### Statistical methods for primary and secondary outcomes {20a}

#### Statistical analysis of the subjective variables

All analyses will be conducted using SPSS24.0 software. Firstly, ANOVAs and chi-square tests will be conducted to determine whether significant differences exist between the different intervention groups for the variables collected (PROMIS and PANAS scales) in the first assessment phase (Time 1) and for the level of immersion when viewing the film clip during the negative mood induction. If differences between groups are found in any of these variables, the variables with statistically significant differences will be included as covariate variables in the following ANOVAs. Secondly, to assess the impact of personal relevance of the images in emotional recovery, a repeated-measures ANOVA and post hoc Bonferroni tests will be performed in a mixed design with type of image (low, medium and high personal relevance groups) and group (young and older) as between-subjects variables and time (pre-test—Time 1—, post-negative emotional induction—Time 2—and post-positive emotional induction—Time 3) as within-subject variables. Finally, to assess the sense of reliving for the three groups of images, a repeated-measures ANOVA and post hoc Bonferroni tests will be performed in a mixed design with type of image (low, medium and high personal relevance groups) and group (young and older) as between-subjects variables and (average score of concentration level recalling the events and average score of the degree of reliving the positive emotions of the remembered events) as within-subject variables.

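### The sense-of-reliving ANOVA tests image type on the average of, and the difference between, the concentration and reliving ratings, so neither omnibus test isolates reliving

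*Protocol article*

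**What the plan says.** The Objectives section ({7}) of the protocol article adds an aim on reliving: "we will also examine the degree of reliving in the autobiographical memories evoked by the three types of images".

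The section on control questions after the pictures defines two separate ratings, each from 0 to 9. One asks the participant to "indicate your level of concentration when recalling the event". The other asks the participant to "indicate to what degree you were able to relive the positive emotions you felt at the moment of the event". Under the intervention description, such questions are answered after each of the six pictures.

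The section on statistical analysis of the subjective variables ({20a}) then states the model: "to assess the sense of reliving for the three groups of images, a repeated-measures ANOVA and post hoc Bonferroni tests will be performed". The between-subjects factors are "type of image (low, medium and high personal relevance groups) and group (young and older) as between-subjects variables". The within-subject variables are the "average score of concentration level recalling the events and average score of the degree of reliving the positive emotions of the remembered events". No time or picture factor is named for this model, and the article states no separate analysis of the reliving rating.

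**The concern.** The objective concerns one quantity, the degree of reliving, compared between three image types. The planned model puts a second quantity, concentration, beside it as the other level of the within-subject factor. Both omnibus image-type tests then mix the two ratings.

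At stake is what a result can be taken to mean. A significant main effect or interaction could come from reliving, from concentration or from both. If images of high personal relevance hold attention better but do not deepen reliving, the planned tests can still be significant and be reported as a difference in reliving. A non-significant interaction, in turn, does not show that reliving is the same in the three arms.

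**Working it through.** The article gives no figure for this analysis, so there is none to reproduce. The check has an exact algebraic part and an illustration.

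**What each test examines.** Let C be a participant's mean concentration rating and R the mean reliving rating, both over the six pictures. With a two-level within-subject factor, the mixed ANOVA separates exactly:

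- the between-subjects effects (image type, age, image x age) are tests on (C + R)/2;
- the interactions of image type or age with the measure are tests on R − C.

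The stated objective needs a test on R.

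**Inputs for the illustration**

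- N = 240, in six cells of 40, and alpha = .05 (Sample size section).
- Partial eta-squared = .06. The Sample size section states this for six repeated measures with correlation .80, so using it for image type on a single rating is an assumption.
- Both ratings have unit variance (assumed). Their correlation r is not given; .3, .5 and .7 are assumed.
- Image type has 2 df; error has 240 − 6 = 234 df.

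**Reliving alone.** f² = .06/.94 = .0638, and λ = .0638 x 240 = 15.32. Power of F(2, 234) is 94.6%.

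**Noncentrality of the planned tests.** Var[(C + R)/2] = (1 + r)/2 and Var(R − C) = 2(1 − r).

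- Only one rating changes. The average moves by half the effect, so λ(main) = 15.32 x 0.25/[(1 + r)/2] = 15.32 x 0.5/(1 + r). The difference moves by the full effect, so λ(interaction) = 15.32/[2(1 − r)].
- Both ratings rise equally. The average moves by the full effect, so λ(main) = 15.32 x 2/(1 + r). The difference does not move, so λ(interaction) = 0.

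| Scenario | Test | r = .3 | r = .5 | r = .7 |
|---|---|---|---|---|
| Only reliving changes | Main effect: λ | 5.89 | 5.11 | 4.51 |
| | Main effect: power | 57% | 51% | 46% |
| | Interaction: λ | 10.94 | 15.32 | 25.53 |
| | Interaction: power | 85% | 95% | 99.7% |
| Both rise equally | Main effect: λ | 23.57 | 20.43 | 18.02 |
| | Main effect: power | 99% | 99% | 97% |
| | Interaction: rejection rate | 5% | 5% | 5% |

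Reliving tested alone has 94.6% power in both scenarios.

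**Only concentration changes.** The formulas are symmetric in C and R. The first block of the table therefore also gives the chance of a significant result when concentration alone differs by the same amount. Here a test on R rejects at its 5% level.

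**Check by simulation.** The 3 x 2 design with 40 per cell was simulated 2,000 times per scenario, with assumed image-type shifts of 0, 0.25 and 0.5 SD and r = .3, .5 and .8.

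- Only concentration shifts: the main effect was significant in 41, 35 and 29% of runs and the interaction in 67, 82 and 100%. Reliving alone was significant in 5, 6 and 5%.
- The two ratings shift in opposite directions: the main effect was significant in only 5, 4 and 6% of runs, although reliving truly differed.

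**The case against.** **Power.** A reader might infer from the main-effect column that the plan loses about half its power for reliving. The documents do not support that. The interaction belongs to the same planned ANOVA and has 85 to 99.7% power when only reliving changes. When both ratings rise equally, the main effect exceeds the 94.6% of the direct test. In each of these two scenarios at least one planned term is likely to be significant. This objection stands, and it limits the point to attribution.

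**Validity of the model.** A reader might also infer that two different items can never be levels of a within-subject factor. Profile analysis does this for items on a common scale, and both ratings run from 0 to 9. The model is computable and valid for what it tests; it is only badly aimed at reliving.

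**A composite target.** The control-question section gives both items one purpose: "To assess the extent to which the participant felt involved in viewing the images chosen to elicit positive affect". If sense of reliving means involvement across both, the main effect tests that composite. This cannot be excluded, but the Objectives section names the degree of reliving, which has its own question.

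**Post hoc tests.** Bonferroni comparisons of image types within the reliving rating would test the objective directly. The plan may intend them, but does not say so.

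**Wording.** The parenthesis that lists the two averages follows no named factor, whereas the preceding model names time. A term may have been lost. The reading used here is the natural one, not the only conceivable one.

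**Averaging over pictures.** Averaging the six ratings is not a fault; the mean is a sound summary of reliving.

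**Conclusion.** The point holds in a limited form. As written, neither omnibus image-type test isolates the degree of reliving, and either can be significant when only concentration differs between arms. The algebra is exact, given that concentration versus reliving is the only within-subject factor. The percentages rest on the assumed effect size, equal variances and assumed correlations.

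This should be fixed, but it does not threaten the trial. A reader might extend it to the analysis of emotional recovery. The documents do not support that: recovery has its own repeated-measures ANOVA with time as the within-subject factor. Reliving is an additional aim of a study that the Trial design section calls exploratory.

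**What to change.** Replace the sentence on sense of reliving in {20a}. Analyse the mean reliving rating over the six pictures as its own outcome in a 3 (image type) x 2 (age group) between-subjects ANOVA, with Bonferroni comparisons of image types on that rating. Analyse the mean concentration rating separately, as a check of engagement. If a composite of the two ratings is really intended, name it as such and keep it apart from the reliving outcome.

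In the simulation, the 3 x 2 ANOVA on reliving alone rejected in 5 to 6% of runs when reliving did not differ. With shifts of 0, 0.25 and 0.5 SD it rejected in 80 to 82%, whatever happened to concentration.

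The cost is a change of analysis wording. Both ratings are already collected, and neither the sample nor the procedures change.

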#### Processing and statistical analysis of objective variables

##### Heart rate variability (HRV) and electrodermal activity (EDA)

Data processing

Cardiovascular and electrodermal activity variables will be measured through blood volume pressure (BVP) and skin conductance, respectively, using the Empatica E4 device. Alternations of the BVP waveform are highly correlated with heart ventricular depolarization and repolarization, thus being suitable to measure heart rhythm [96]. BVP and SC will be recorded at a sampling rate of 100 Hz and 4 Hz, respectively. Once data are acquired, BVP and SC signals will be processed to reduce noise. To avoid noise, different filters will be applied to both signals. Specifically, for the BVP signal, baseline drift will be removed by carrying out a 0.5-Hz cut-off-high-pass, linear phase finite impulse response (FIR) filter. Then, a 30-Hz cut-off low-pass, linear-phase FIR filter will be used to eliminate high-frequency noise and power-line interferences. Additionally, peaks related to pulse pumping will be located on BVP signals using a robust and reliable peak detection algorithm, capable of dealing with movement artefacts and signal morphologies [97]. Finally, interbeat intervals (IBIs) will be derived from the peak-data series.

Related to the SC signal, SC morphology is the result of two independent components: a fast-changing skin conductance response (SCR), overlapped with a slowly changing skin conductance level component (SCL). The SCL component ranges from 0 to 0.05 Hz, while SCR ranges from 0.05 to 1.5 Hz. Each SC signal will be filtered by applying a 1.5-Hz cut-off low-pass FIR filter to decrease noise generated during the acquisition.

Regarding heart rhythm, the IBI data series will be transformed to obtain the heart rate (HR) measured in beats per minute (BPM). Then, the HR metric will be partitioned into 5-s equally separated segments. Finally, the mean HR will be stored and used subsequently in the statistical analysis. A similar procedure will be carried out with the SC processed series. The data series will first be divided into equal segments lasting 5 s, and the mean of each segment will be recorded for subsequent analysis.
b)Data analysis

We will calculate the mean SCL and HR values recorded for 4 min before the start of the negative mood induction procedure. These will be compared with the maximum scores obtained in the experimental phases (negative mood induction—viewing film clip—and emotional recovery using images). Independently for SCL and HR variables, repeated-measures ANOVA and post hoc Bonferroni tests will be performed in a mixed design with group (low, medium and high personal relevance groups) as between-subjects variable and time (pre-test—Time 1; post-negative emotional induction—Time 2; and postpositive emotional induction—Time 3) as within-subject variables.

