##### Autonomic nervous system

As previously mentioned, emotions involve psychophysiological processes, and thus generate changes in variables such as heart rate and blood pressure [68] or galvanic skin response [69].

A number of studies have reported higher heart rate variability (HRV) in older adults as self-reported positive emotion and well-being increase [70], with high HRV being associated with greater emotional well-being and better emotion regulation [71–73]. Then, the health benefits of positive emotions on health may derive from reduced cardiovascular activation associated with decreased sympathetic nervous system (SNS) activation and an increase in activation of the parasympathetic nervous system (PNS) [74]. Furthermore, positive emotions facilitate cardiovascular recovery following negative emotions [75]. Low heart rate has been associated with pleasant or relaxed emotional states, while heart rate accelerations occur in response to intense emotional states, sexual arousal or mental effort [76].

Furthermore, electrodermal activity (EDA), or galvanic skin response (GSR), has been associated with SNS activity [77, 78]. Studies such as that by Codispoti et al. reported higher skin conductance response to exposure to emotional pictures [79]. The use of EDA is highly effective in measuring the level of an individual’s emotional arousal, regardless of the emotional valence of the stimuli, since it is able to quantify changes in the SNS [80]. Various studies have identified changes in EDA (increase in peaks) following exposure to images taken from the IAPS [81].

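### The variable analysed as SCL still carries part of the protocol's own SCR band, and the SCR itself is recorded but never extracted or tested

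*Protocol article*

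**What the plan says.** All but the last item below come from the section on heart rate variability and electrodermal activity, under its data processing and data analysis parts.

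- **Components.** The protocol states that "SC morphology is the result of two independent components", a fast response (SCR) on top of a slow level (SCL), and gives their limits: "The SCL component ranges from 0 to 0.05 Hz, while SCR ranges from 0.05 to 1.5 Hz".
- **Recording.** "BVP and SC will be recorded at a sampling rate of 100 Hz and 4 Hz, respectively".
- **Filter.** "Each SC signal will be filtered by applying a 1.5-Hz cut-off low-pass FIR filter to decrease noise generated during the acquisition". No other filter or decomposition of skin conductance is stated.
- **Reduction.** "The data series will first be divided into equal segments lasting 5 s", and the mean of each segment is kept.
- **Analysis.** For baseline: "We will calculate the mean SCL and HR values recorded for 4 min before the start of the negative mood induction procedure". For the film and picture phases: "These will be compared with the maximum scores obtained in the experimental phases". Repeated-measures ANOVAs are then planned for SCL and HR, and for no other variable from this device.
- **Rationale.** The background section on the autonomic nervous system supports EDA with a cited study of skin conductance responses to emotional pictures, and adds: "Various studies have identified changes in EDA (increase in peaks) following exposure to images taken from the IAPS".

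**The concern.** The protocol draws the line between tonic and phasic activity at 0.05 Hz, but no processing step acts at that line. What reaches the ANOVA is filtered and averaged total skin conductance under the name SCL.

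Two things are at stake. First, a difference in this variable between image types could come from more frequent or larger SCRs with a steady tonic level, or from a shift in tonic level, and the planned analysis could not tell which. Second, the background rests the use of EDA with pictures largely on phasic responses, yet no SCR count, peak or amplitude is defined or tested. EDA is meant to substantiate the self-reports, and it does this less well if the component being reported is unclear.

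**Working it through.** The protocol gives no figure of its own to reproduce. The check compares the stated bands with what the stated steps let through.

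**Inputs from the protocol.** SCL 0-0.05 Hz; SCR 0.05-1.5 Hz; sampling at 4 Hz; low-pass FIR at 1.5 Hz; 5-s means (4 × 5 = 20 samples each); phase summary = maximum; picture phase = 6 pictures × 1 min = 360 s.

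**Assumptions.** The number of filter taps is not stated, so 21, 41 and 81 were tried. SCR shapes are bi-exponential with rise constants of 0.3-0.75 s and decay constants of 2-4 s.

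**Step 1: the 1.5 Hz filter.** At all three tap numbers the gain is about 1.00 from 0.01 to 1.0 Hz and 0.50 at 1.5 Hz. Essentially all of both bands passes.

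**Step 2: the 5-s mean.** Its gain at frequency f is |sin(5πf) / (5πf)|.

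| f (Hz) | Calculation | Gain |
|---|---|---|
| 0.05 | sin(0.25π) / 0.25π = 0.707 / 0.785 | 0.90 |
| 0.089 | half-power point | 0.71 |
| 0.10 | sin(0.5π) / 0.5π = 1 / 1.571 | 0.64 |
| 0.15 | sin(0.75π) / 0.75π = 0.707 / 2.356 | 0.30 |
| 0.20 | sin(π) / π | 0 |
| above 0.20 | side lobes | at most about 0.21 |

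There is no cut at 0.05 Hz. For the assumed SCR shapes, 33-42% of the power in the SCR band survives, so 58-67% is removed.

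**Step 3: effect on the analysed statistic.** One SCR of height 1 raises the largest 5-s mean by 0.28-0.73, depending on its shape and where it falls in the segment.

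**Step 4: would a 0.05 Hz low-pass be enough?** Take an SCR of 0.5 µS with constants 0.75 s and 4 s, arriving at random on a flat tonic level.

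- *Phase mean.* The raw curve peaks at 0.552, so the area of one SCR is 0.5 × (4 − 0.75) / 0.552 = 2.94 µS·s. At 2, 4 and 8 SCRs per minute the mean rises by rate × 2.94 / 60 = 0.10, 0.20 and 0.39 µS. A low-pass has gain 1 at zero frequency, so it leaves these values unchanged. By the protocol's frequency definition they belong to SCL.
- *Phase maximum, simulated over 360 s.*

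| SCRs per min | As written (µS above tonic) | After 0.05 Hz Butterworth low-pass | Fall |
|---|---|---|---|
| 2 | 0.65 | 0.51 | 22% |
| 4 | 0.91 | 0.73 | 20% |
| 8 | 1.31 | 1.11 | 15% |

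With an FIR low-pass the fall is 18-25%. The maximum therefore follows the SCR rate in both cases. The low-pass makes the variable match the stated band, but it does not separate tonic from phasic change, because an SCR also has energy below 0.05 Hz.

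**The case against.** The strongest reply has four parts.

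- **The 5-s mean already acts as a low-pass.** This stands. Looking only at the 1.5 Hz filter, a reader might infer that the whole SCR band enters the variable. It does not: content above 0.2 Hz is largely removed, and the contamination is partial.
- **SCR is not lost.** This also stands. A reader might infer that the picture-evoked response is never measured. The raw signal is kept at 4 Hz and SCR can be derived from it. What is absent is its extraction and testing.
- **A level measure is defensible.** Each picture is viewed for a minute of sustained recall, and the background also describes EDA as an index of arousal level. This supports analysing SCL. It does not support giving the name SCL to a variable that falls outside the protocol's own definition of it.
- **The article may have condensed a decomposition step.** This is possible, but the article gives the sampling rate, the bands, the filter and its purpose, and the segment length. As written, that chain does not lead to the variable that is tested.

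A reader might also take the phase-mean shifts of 0.10-0.39 µS as evidence of harm. They are not: a 0.05 Hz low-pass leaves them unchanged, and the phase mean is not the planned statistic.

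**Conclusion.** The point holds as a mismatch between the stated bands, the stated processing and the name of the analysed variable. The variable retains part of the SCR band, mainly 0.05-0.15 Hz, and the phase maximum responds to it. The SCR is recorded but has no planned analysis.

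The filter gains follow from the protocol's own figures. The share of power retained and the simulated maxima rest on assumed SCR shapes, size and rates, and only illustrate the order of magnitude.

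The consequence is limited to how the EDA result is read. The trial is described as exploratory, and the objectives section gives the physiological measures a supporting role. Nothing here affects the PANAS analysis or makes the EDA recording unusable. The change is worth making before analysis but does not threaten the main result.

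**What to change.** In the data processing part, after the 1.5 Hz noise filter and before the 5-s segmentation, add a named tonic/phasic decomposition of the 4 Hz signal and take SCL from the tonic series. It has to come before the segmentation because 5-s means form a series at 1/5 = 0.2 Hz, which folds any remaining content above 0.1 Hz into lower frequencies.

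In the data analysis part, add one SCR measure, for example peaks per minute or mean amplitude in the film and picture windows, in the same repeated-measures model.

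If no decomposition is adopted, call the variable total skin conductance throughout and do not interpret it as SCL. A 0.05 Hz low-pass alone would repair the label but would not let tonic and phasic change be told apart.

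The cost is one extra processing step and one extra supportive test, both from data already to be recorded. Renaming alone costs nothing but leaves the SCR untested.

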**Methods:**

The participants, 120 older adults aged 65 and over and 120 young adults aged between 18 and 35, of both sexes and without depressive symptoms, will be induced to a negative mood state by means of viewing a film clip. Following the negative mood induction, the participants will be shown positive images according to experimental group to which they were randomly assigned (high personal relevance: personal autobiographical photographs; medium personal relevance: pictures of favourite locations associated with specific positive autobiographical memories; and low personal relevance: positive images from the International Affective Picture System). We will analyse the differences in subjective (responses to questionnaires) and objectives measures (EEG signal, heart rate variability and electrodermal activity) between the groups before and after the induction of negative affect and following the recall of positive memories.

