The objective measures of emotion (EEG, EDA and HRV) will be used to substantiate the effects of emotion induction mechanisms observed in self-evaluations.

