##### EEG signal

Data processing

The EEG recordings will be analysed off-line using custom software written in MATLAB. This custom software will be based on EEGLAB tools [98]. EEG functions will be used to clean the EEG-data. The EEG data will be segmented based on the event types. Fast Fourier transformation will be applied to an EEG epoch consisting of the time windows of 30 s each after the onset of the stimulus (film and images). Fourier transformed signals will then be averaged across event types. For further analysis, left frontal (F3, F7, FC5) and right frontal (F4, F8, FC6) electrode pools will be formed by averaging the frequency distributions of these signals. The mean magnitude of delta (0.5–4 Hz), theta (4.5–7.5 Hz), alpha (8–12.5 Hz), beta (13–30 Hz) and gamma (30.5–60 Hz) frequency band activities will be calculated for each participant during each event type.
b)Data analysis

A repeated-measures ANOVA will be performed to examine the possible effects of the intervention group (between-subjects variable) and time (within-subject variable) on the frequency band oscillations from frontal electrodes and on laterality (left vs right) by also examining the frequency band oscillations.

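### Heart rate variability is named as an objective outcome but only heart rate is processed and tested, and the before-induction EEG comparison promised in the abstract has no pre-induction epoch

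*Protocol article*

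**What the plan says.** **Outcomes promised.** The Methods part of the abstract says the trial will analyse "differences in subjective (responses to questionnaires) and objectives measures (EEG signal, heart rate variability and electrodermal activity) between the groups", and places the comparison "between the groups before and after the induction of negative affect and following the recall of positive memories". The Objectives section gives these measures their role: "The objective measures of emotion (EEG, EDA and HRV) will be used to substantiate the effects of emotion induction mechanisms". Data management again lists HRV, with electrodermal activity and EEG, among the processed measures to be entered in the SPSS file. The section on cardiac and electrodermal processing carries HRV in its heading.

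**Cardiac processing and analysis.** That section filters the pulse signal and detects peaks. It then states: "Finally, interbeat intervals (IBIs) will be derived from the peak-data series". The intervals are converted to heart rate in beats per minute and cut into 5-s segments, and the step closes: "Finally, the mean HR will be stored and used subsequently in the statistical analysis". The data analysis part takes a 4-min pre-induction mean of skin conductance level (SCL) and heart rate, compares it with the maxima in the film and picture phases, and runs a repeated-measures ANOVA separately for SCL and for heart rate.

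**EEG processing and analysis.** The EEG section applies the Fourier transform to "time windows of 30 s each after the onset of the stimulus (film and images" and computes band magnitudes for each event type. Its ANOVA has time as a within-subject factor, but the levels of time are not listed.

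**The concern.** Two promised comparisons do not survive the trace from outcome to analysis.

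First, HRV and mean heart rate are different quantities. The background on the autonomic nervous system ties HRV to the construct under study, "with high HRV being associated with greater emotional well-being and better emotion regulation". If only heart rate is analysed, there will be nothing to report under the HRV label. The risk is that a heart rate result is presented as HRV evidence, or that a variability index and its window are chosen after the data have been seen.

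Second, a before-induction EEG comparison needs an EEG value from before the film, and every epoch that the EEG section defines follows stimulus onset. EEG is meant to back up the self-reported induction effect, but as specified it has nothing to compare the film with.

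**Working it through.** The plan states no figure to reproduce here. The check follows each promised measure through processing to test.

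| Measure | Promised in | Value formed | Pre-induction level defined? | Tested? |
|---|---|---|---|---|
| Electrodermal activity | Abstract, Objectives, Data management | SCL, 5-s segment means | Yes, 4 min | Yes |
| HRV | Abstract, Objectives, Data management, section heading | None; heart rate formed instead | No (heart rate only, 4 min) | No |
| EEG | Abstract, Objectives, Data management | Band magnitudes per event type (film, images) | No | Yes, with the levels of time unlisted |

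**Can stored mean heart rate stand in for HRV?** Take two assumed interbeat series, for illustration only.

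- Series A: every interval is 800 ms. Heart rate = 60 / 0.800 = 75.0 bpm. Successive differences are all 0, so RMSSD = 0 ms.
- Series B: intervals alternate between 860 and 740 ms. The mean interval is (860 + 740) / 2 = 800 ms, so heart rate is again 60 / 0.800 = 75.0 bpm. Each successive difference is ±120 ms, so RMSSD = √(120²) = 120 ms.

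Run through 5-s segments, the mean heart rate is 75.0 bpm for A and 74.98 bpm for B. The standard deviation of B's segment means is only 0.39 bpm. If rate is instead computed beat by beat and then averaged, B gives (60/0.860 + 60/0.740) / 2 = (69.77 + 81.08) / 2 = 75.42 bpm, still within about 0.4 bpm of A. Either way, series with RMSSD of 0 and 120 ms look almost the same once reduced to 5-s mean heart rate.

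**Which EEG contrasts remain?** Write B for before induction, F for film and P for pictures. Three times give three pairwise contrasts: F − B (induction), P − F (recovery from the film) and P − B (return to the starting level). The EEG section defines F and P only, so P − F is available and the two contrasts involving B are not.

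**Does the wording about 30-s windows change this?** It can mean one window per stimulus, or successive windows. On the second reading the 7-min film gives 420 / 30 = 14 windows and each 1-min picture gives 60 / 30 = 2. On both readings every window follows onset, so neither supplies B.

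**The case against.** **The data may well allow both analyses.** Interbeat intervals are derived, the Empatica E4 description says the device can measure HRV, and the devices are worn during the experimental task. This stands. A reader might infer that the HRV and EEG comparisons cannot be made at all; the documents show only that the processing as written does not make them.

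**Heart rate has its own rationale.** The section introducing objective measurement names heart rate, and the autonomic background links low heart rate to pleasant or relaxed states and acceleration to intense ones. This also stands: analysing heart rate is legitimate. A reader might infer that a stated HRV hypothesis goes untested, but the objectives state none. They give HRV, EDA and EEG only a substantiating role.

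**An article condenses.** Exact epochs and factor levels are often left to a fuller document. That carries some weight for EEG, where two levels of time are inferred because none are listed. It carries less for the cardiac pipeline, which is given down to filter cut-offs and segment length and then names heart rate as the analysed variable. For both signals the point is a conflict between statements in the article, not an omitted detail.

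**Recovery is still addressed.** All groups see the same film, so film versus images by randomised group speaks to the main question, and the check on induction is assigned to PANAS. This stands and limits the loss to EEG evidence on induction and on return to baseline.

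**A stronger reading of the EEG windows.** A reader might infer that the film is represented only by its opening 30 s and so amounts to a baseline in disguise. The wording also permits successive windows, and nothing in the document says how quickly the clip takes effect. That inference is not supported.

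**Conclusion.** The point holds as a contradiction within the protocol article. HRV is promised in the abstract, the objectives, data management and a section heading, yet no variability index is formed and neither of the two specified autonomic ANOVAs (SCL, heart rate) tests one. Followed as written, the plan gives no HRV result. For EEG, the promised before-induction level is undefined, leaving one of three pairwise time contrasts.

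The EEG conclusion assumes that the film and image epochs named in the EEG section are the only ones intended. The heart rate illustration uses assumed series and shows only that mean rate does not determine variability; it makes no forecast for this trial.

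The weight is moderate. These are supporting measures in a study that calls itself exploratory. SCL has its baseline, and the PANAS analysis is untouched. It is worth correcting before the data are seen, because the choice of index, window and epoch is otherwise open.

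**What to change.** **Cardiac.** From the interbeat intervals already derived, compute one prespecified variability index, such as RMSSD, over equal-length windows in the 4-min baseline, the film and the picture phase. Analyse it with the same group-by-time model as heart rate. Use the same summary at all three times, since the heart rate comparison sets a baseline mean against phase maxima. Because control questions follow each 1-min picture, the longest uninterrupted picture window is 60 s. Windows of that length would give 240 / 60 = 4 in the baseline, 420 / 60 = 7 in the film and 6 in the picture phase. Alternatively, replace HRV with heart rate in the abstract, objectives, data management and heading.

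**EEG.** Add a pre-film baseline epoch, state which 30-s film windows are used, and list three levels of time. This assumes that EEG is recorded in the 4-min pre-induction period, which the protocol states for SCL and heart rate only; that should be confirmed. Alternatively, withdraw the before-induction EEG comparison from the abstract.

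**Cost.** A processing script and some wording, with no added assessments if EEG is already running in the baseline period. The downside is that some windows will be lost to artefact rejection in the pulse signal, so a rule for unusable windows should be set in advance. Renaming the outcome costs only wording, but gives up the HRV evidence.
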